### Secondary Analyses

Secondary analyses of all outcomes will be done in the per-protocol analysis set.

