The diagnostic PSMA-ligand ^68^Ga-PSMA-11, first introduced in 2011, has become the predominantly used PSMA-tracer in Switzerland. Although ^68^Ga-PSMA-11 reveals PC lesions often with excellent contrast, the short half-life of the isotope ^68^Ga (68min) creates handling difficulties and its excretion via the urinary system can complicate the diagnosis of local recurrences where bladder activity can obscure the prostate fossa. Recently, a novel PSMA-ligand has been introduced for PET-imaging (PSMA-1007) offering several potential advantages. Firstly, PSMA-1007 can be labelled with ^18^F, which has a longer half-life, thereby offering greater flexibility in the planning of scans. This longer half-life simplifies delivery of the radioisotope to peripheral clinics and the clinical routines involved in its use. Secondly, the physical properties of ^18^F potentially offer higher imaging resolution. Thirdly, unlike ^68^Ga-PSMA-11, ^18^F-PSMA-1007 often exhibits minimal excretion via the urinary bladder within the first 2-3h post injection (p.i.) tracer. This has the potential to improve the detection of local relapses adjacent to the urinary bladder wall.

There are currently no published prospective head-to-head studies comparing these two tracers in recurrent PC. These tracers are the only ones available in Switzerland. Because of this lack of data, there are no clear recommendations about which tracer to use and it which situation.

This study aims to fill this gap and provide comprehensive data with the potential to improve the diagnosis of PC. By providing robust data comparing the two tracers, such data will also provide guidance to clinicians faced with the scenario of an initially negative ^68^Ga-PSMA-11 PET as to the diagnostic utility of an additional ^18^F-PSMA-1007 PET, or vice-versa, and in which scenarios repeated scanning may be justified. In this regard, the impact of head-to-head data for these two tracers cannot be underestimated and is likely to yield significant influence on clinicians in their choice of PSMA-tracer and how they perform these scans. Such data would therefore have the potential to reduce the total radiation dose to patients by reducing unnecessary repeat scanning, and would also reduce costs to the health care system. This latter point is non-trivial considering prostate cancer’s high prevalence.

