# STUDY DESIGN

## General study design and justification of design

Given the complexity of conducting nuclear imaging procedures and the multiple factors that must be borne in mind when attempting a fair and scientific comparison of the two substances, we outline the reasoning behind our numerous considerations here.

It is known that androgen deprivation therapy (ADT), a commonly prescribed treatment in recurrent prostate cancer, can affect PSMA expression of castration sensitive PC lesions in PSMA-PET/CT [27], resulting in unpredictability of the PET results. We therefore exclude patients undergoing ADT 6 months prior to the scans.

Forced diuresis is recommended in ^68^Ga-PSMA-PET/CT [17] due to high levels of tracer accumulation in the bladder, which potentially obscures lesions adjacent to the bladder, as shown in figure 3. This also facilitates a fair comparison between ^68^Ga-PSMA-PET/CT and ^18^F-PSMA-1007, which as outlined above, does not exhibit relevant urinary excretion within the first 2-3 hours p.i. [28]. Administration of intravenous (i.v.) furosemide (20 mg 30min before the final scan) and oral hydration (1L) is therefore included in the protocol for ^68^Ga-PSMA-11, and has been shown to reduce urinary bladder activity, which improves the visualisation of lesions adjacent thereto (see figure 3).

Identifying the optimal time-point at which to administer hydration and diuretics is hampered by the lack of data regarding the optimal imaging protocol. Forced diuresis too early following injection of the radiotracer is to be discouraged due to reduction of tracer availability at later time-points (2h) [22]. Given that increasing uptake over time is to be expected for PC lesions [23, 29], we favour application of diuretics as late as reasonably practical. In contrast, ^18^F-PSMA-1007 does not exhibit relevant urinary excretion within the first 2-3 hours after injection, thus making application of furosemide unnecessary [28].

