## Determination of Sample Size

Power was determined using Monte Carlo simulations with 1000 repetitions and the following assumptions:

- Marginal probabilities: 80% of the patients are positive for tracer A and 80% are positive for tracer B
- Both tracers are applied to each patient
- Non-inferiority design with a one-sided alpha of 2.5%
- Non-inferiority margin of -10% (clinically acceptable margin in detection rate, balanced against the requirements for clinically realistic number of patients). We justify this margin as being less than 50% of the margin reported for superiority (22%) in a prospective trial published for ^68^Ga-PSMA-11 versus the first-generation tracer ^18^F-Choline [22].
- Non-inferiority is concluded if the lower limit of a 95% confidence interval (Wald with Bonett–Price Laplace adjustment) for the difference in the proportion of tracer-positive patients (new tracer – old tracer) is larger than the non-inferiority margin
- A pragmatic assumption is made regarding the correlation of the paired measurements. Limited data are available for this, given the dearth of comparative studies. Neither retrospective analyses [28] nor limited pilot studies [17, 27] have demonstrated any difference in detection rate. We take a worst-case scenario, and assume that both tracers are positive for 75% of the patients.

Data was simulated using function rmvbin from R package bindata [29]. With 100 patients we will have a power of 85% to detect non-inferiority.

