### Datasets to be analysed, analysis populations

The full analysis set will include all randomised patients. They will be analysed according to the group they were randomised to regardless of the tracer actually used according to the intention-to-treat principle. We will also define a per-protocol analysis set that excludes major protocol violations.

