### Primary Analysis

The primary outcome (proportion of patients with PSMA-positive pathological lesions) will be compared between tracers using an absolute risk difference (new tracer minus old tracer) with a one-sided lower 95% confidence interval (CI) for paired proportions (Wald with Bonett–Price Laplace adjustment). If the lower limit lies above -10%, we will claim non-inferiority. Proportion of pathologic scans will be based on majority consensus reads.

The number of PSMA-positive lesions defined as pathological, benign and uncertain in each region will be analysed using separate mixed-effects Poisson regression models with tracer as fixed covariate and nested random effects for patient and region. We will report incidence rate ratios with 95% CI and p-values. As a sensitivity analysis we will compare the number over all regions using the Wilcoxon signed-rank tests and the Mann-Whitney statistic with 95% CI.

Inter-reader reliability will be analysed on the region-level based on the number of benign, pathological and uncertain lesions determined by each reader. We will calculate Krippendorff’s alpha with a ratio difference function and bootstrap 95% CI separately for each tracer.

Lesion-based PPV will be calculated for each tracer as the proportion of pathological lesions confirmed pathological during follow-up among all lesions with a known state and will be presented with 95% Wilson score CI. Using all lesions with a confirmed status during follow-up, the two tracers will be compared using McNemar’s test and an absolute risk difference with 95% confidence interval.

The semi-quantitative tumour to background ratio will be summarized on a region-level (i.e. using the mean over all positive lesions per region) and analysed using a linear mixed-effects regression model with tracer as fixed covariate and patient and region as nested random effects. The mean difference with 95% CI will be reported.

For the subset of patients with additional parametric imaging data (N=10) the planned analysis of parametric imaging parameters (see first secondary endpoint) is planned prior to completion of the study. This exploratory analysis of this secondary endpoint will not assess the primary endpoint and will not influence further trial conduct or further trial process.

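### The non-inferiority claim rests on the full analysis set, and the planned per-protocol result has no say in it, so deviations that cost 68Ga positive calls can help the claim through

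*Protocol*

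**What the plan says.** Section 11.4.1 defines a full analysis set of all randomised patients, analysed by randomised group whatever tracer was given. It adds: "We will also define a per-protocol analysis set that excludes major protocol violations". Section 11.4.2, like the synopsis, gives a single decision rule: "If the lower limit lies above -10%, we will claim non-inferiority". It does not say in which set that limit is computed. Section 11.4.3 then states: "Secondary analyses of all outcomes will be done in the per-protocol analysis set". Read together, the full set carries the claim. The primary outcome is also analysed per protocol, but only as a secondary analysis, and nothing says what follows if the two results differ.

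On the comparator, section 3.1 says the short half-life of 68Ga "creates handling difficulties and its excretion via the urinary system can complicate the diagnosis of local recurrences". Section 6.1 says the diuretic and oral hydration step "is therefore included in the protocol for ^68^Ga-PSMA-11, and has been shown to reduce urinary bladder activity". Section 3.5 requires no such preparation for 18F-PSMA-1007.

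**The concern.** In a superiority trial, keeping poorly executed assessments usually dilutes the effect and is conservative. In a non-inferiority trial it need not be. Here each patient has both scans, and the difference is new minus old. If a 68Ga scan is badly executed and a positive patient is read as negative, a both-positive pair becomes new-only, or an old-only pair becomes negative on both. Either change raises the difference.

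Diuresis is the clearest route. It is required for 68Ga only, and section 6.1 (legend to figure 3) describes a lesion in one patient that could not be told from bladder activity without it. A complete, correctly assigned pair with such a deviation stays in the deciding set. The full-set limit could then clear -10% while the per-protocol limit does not, and the protocol would still claim non-inferiority.

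**Working it through.** **Inputs from the protocol.** N = 100; margin -10 points; 80% positive on each tracer and 75% on both, hence 5% discordant each way; one-sided alpha 2.5%; stated power 85% (all section 11.2). Interval: "Wald with Bonett–Price Laplace adjustment" (section 11.4.2). That section also writes "with a one-sided lower 95% confidence interval (CI) for paired proportions", which taken literally is alpha 5%. I use z = 1.96, because that is what reproduces the stated power.

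**Formula.** With n10 new-only and n01 old-only pairs: p10 = (n10+1)/(N+2), p01 = (n01+1)/(N+2), d = p10 - p01, and lower limit L = d - 1.96 × √[(p10 + p01 - d²)/(N+2)].

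**The plan's own figure.** Exact enumeration of the discordant counts at 5%/5% gives power 86.5%. A 1000-repetition simulation gives 84.9%. The stated 85% is reproduced. (At one-sided 5% it would be 92.0%.)

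**One pair can separate the two sets.**
- Suppose the true findings are 5 new-only and 8 old-only in 100, and one both-positive patient has a deviant 68Ga scan read as negative.
- Full set, 6 versus 8 of 100: d = 7/102 - 9/102 = -0.0196; L = -0.0196 - 1.96 × √(0.1565/102) = -0.096. Claim made.
- Per protocol, 5 versus 8 of 99: d = 6/101 - 9/101 = -0.0297; L = -0.0297 - 1.96 × √(0.1476/101) = -0.105. No claim.

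**False-claim rate.** Assumed truth: old 80%, new 70%, 5% new-only, 15% old-only, 65% both positive. Of the 100 pairs, k have a deviant 68Ga scan, and each such scan loses a positive call with probability q. Both k and q are assumptions. The expected difference is -10 + 0.8 × k × q points; for k = 10 and q = 0.5 it is -10 + 4 = -6. The per-protocol set is assumed to remove exactly the k patients. Rates are by simulation; repeat runs differ by about 0.1 point.

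| k | q | expected difference (points) | full set decides | both sets required |
|---|---|---|---|---|
| 0 | – | -10.0 | 2.7% | 2.7% |
| 5 | 10% | -9.6 | 3.3% | 2.3% |
| 10 | 10% | -9.2 | 4.0% | 2.2% |
| 5 | 30% | -8.8 | 4.7% | 2.5% |
| 10 | 30% | -7.6 | 7.5% | 2.6% |
| 5 | 50% | -8.0 | 6.3% to 6.4% | 2.7% |
| 10 | 50% | -6.0 | 12.8% to 12.9% | 2.8% |

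The per-protocol limit alone stays at about 2.8%.

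**If the per-protocol set misses some deviant scans.** With k = 10 and only half of them excluded, the joint rule gives 4.4% at q = 30% and 6.4% at q = 50%.

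**Deviations on the other side.** If the tracers are truly equal and 5% of 18F positives are lost, power falls from 86.5% to 37%. With a true -10 points and an equal 5% loss on both tracers, false claims are 3.3%.

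**Cost of the joint rule.** Under the planning assumptions, with exclusions unrelated to the findings, power for both sets is about 83% with 5 exclusions and 80% with 10.

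**The case against.** A full-set decision with a supportive per-protocol analysis is an accepted convention, and the protocol does not contradict itself. The per-protocol result of the primary outcome is planned, so a reader who infers that a discordant result would go unseen is mistaken. What stands is that it would have no consequence. An unseen SAP may well list the major violations, but one that gave the per-protocol set a deciding role would contradict 11.4.3.

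A reader might also infer that the protocol predicts frequent comparator failures. It does not:
- Section 3.5 names replacement producers working under the same conditions, sets the 68Ga activity with supply in mind and lengthens acquisition to compensate.
- Furosemide is part of routine practice (3.5), and patients who cannot take it are excluded (7.1).
- Administration is directly observed (8.4), and two technologists check each dose (9.2.4.1).

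Nor does every deviation favour the new tracer. The 2 h window applies to both, and section 3.5 itself says later imaging improves contrast, so a late 68Ga scan need not lose a call.

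High loss rates are unsupported too. The endpoint is per patient and by majority of three readers, so a patient with a second pathological lesion away from the bladder stays positive. These points limit the likely size. They do not give the per-protocol result a role in the claim.

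The usual objection to per-protocol sets, lost comparability between arms, is weak here: excluding a patient removes both of his scans.

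**Conclusion.** The point holds as a weakness of the decision rule. One limit, in the full set by inference, decides the claim, and a failed per-protocol limit cannot block it. The bias runs towards non-inferiority only for deviations that cost 68Ga calls; deviations that cost 18F calls run against it.

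The size is illustrative. It is small at 10% call loss (3.3% to 4.0%, against 2.7% with no deviations) and becomes material only at loss rates of 30% to 50%, for which the protocol gives no support. The 7.5% and 13% figures should therefore not be read as this trial's error rate. The protection from the joint rule depends on the per-protocol set actually removing the deviant scans.

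**What to change.** In section 11.4.2 and the synopsis, state that non-inferiority is claimed only if the lower limit lies above -10% in both the full analysis set and the per-protocol set. In section 11.4.3, take the primary outcome out of the purely secondary per-protocol analyses. Classify major violations before the central reads are opened, against limits the protocol already sets: administered activity within 15%, imaging within 10 minutes of 2 h, furosemide with 68Ga, and no change of treatment between scans. Restate the power in section 11.2 and the synopsis for the joint rule.

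The cost is power: about 83% with 5 exclusions or 80% with 10, below the stated 85%. If that loss is accepted, no extra patients are needed. The per-protocol analysis is already planned, and no clinical procedure changes.

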### Subgroup analyses

No subgroup analyses are planned.

### Interim analyses

None planned.

### Safety analysis

The number and severity of adverse events (up to 48h post exam) will be summarised by tracer using descriptive statistics. All serious adverse events will be listed.

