## Dose Rationale

^68^Ga-PSMA-11 examination protocol

We will apply, in accordance with the “Fachliteratur”, 150 MBq ± 15% of ^68^Ga-PSMA-11.

Ideally, the dose applied would be the same as that of the comparator. As a result of a change in production of ^68^Ga-PSMA-11 from the Unilabor Bern to SWAN Isotopen AG, interruptions and periods of non-production are expected and have been experienced. In these cases, the radiopharmaceutical will be sourced from the Radiopharmazie of the USZ and from EURO-PET-GmbH (Freiburg im Breisgau, Germany). Here the radiopharmaceutical is produced under identical conditions, and both producers hold TLD licences. Higher doses (300 MBq) cannot be guaranteed as a result of the long logistics chain, and in any case, would be outwith the Fachliteratur. We will therefore apply 150 MBq but increase the acquisition time to obtain the same count statistics as if 300 MBq had been applied (this is equivalent to the photography concept of “exposure”). The “Fachliteratur” for ^18^F-PSMA-1007 defines, without any basis in evidence, an acquisition time of 2h; this is not specified in the literature for ^68^Ga-PSMA-11, although later acquisitions are known to lead to increased tumour-to-background ratios [18].

For all patients PET/CT examinations will be performed at 2h (± 10min) post application of the radiotracer as described, with image acquisition from the thighs to the skull base, as per institutional protocol. Before each scan, the patients will be asked to empty their bladder.

As described above, given the urinary excretion of ^68^Ga-PSMA-11 which can obscure lesions contiguous with the bladder, furosemide is given as per routine clinical protocol. 20mg of furosemide will be given intravenously (i.v.) 20-30 min prior to the final scan [19]. 1L of water will be provided to the patients to drink.

^18^F-PSMA-1007 examination protocol

We will inject a dose of 300 MBq ± 15% of ^18^F-PSMA-1007 intravenously with PET/CT examinations 2h post application of radiotracer as described in the “Fachinformation” (Appendix A) for ^18^F-PSMA-1007. PET/CT will be performed from thighs to skull base, as per institutional protocol. No further preparations are necessary due to the limited renal excretion of this tracer. The patient will empty his bladder prior to each scan.

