## Secondary Outcomes

- Intra-individual comparison of the parametric imaging parameter K*_D_* (measure of tracer affinity) for the two radiotracers for n=10 patients.
- The number of pathological, benign and uncertain lesions for each tracer in five regions (prostate bed, pelvic lymph nodes, extra-pelvic lymph nodes, bone, or other organs) classified by six blinded readers (three for each tracer) using previously published interpretation guidelines (PSMA-Rads 1.0)
- Inter-reader reliability between the three readers for each tracer on the level of the region with respect to three categories (pathological, benign, uncertain).
- The region-based positive predictive value (PPV), i.e. the percentage of pathological lesions that are confirmed pathological at the 6 month follow-up (based on the subset of patients and lesions with follow-up data at 6 months).
- Tumour visibility will be compared by means of uptake values (SUV) as well as tumour to background contrast in a lesion based analysis. The tumour to background ratio (TBR) is defined as lesion SUV and SUV÷ SUV of reference background region, where the background uptake is defined by convention as the left gluteal musculature.
- Number and severity of adverse events per tracer (up to 48h follow-up, see below)

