### Assessment of safety outcomes

Any adverse events will be recorded. Tolerability of the radiotracer will be followed up 48 hours following administration of the radiotracer by the study nurse, who will have access to a physician should any questions arise. Any AE will be assessed by a physician-investigator.

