9.2.4.1 Adverse events

Any adverse event will be recorded in the individual’s clinical notes as per routine clinical usage: time of onset, duration of event, type of event, symptoms, actions taken, time to resolution, assessment of intensity. The results of any root-cause-analysis will be recorded.

Normal routine clinical procedures will be in place for the avoidance of errors in radiopharmaceutical dose and route of administration (each dose will be checked for quality in accordance with routine clinical procedures). Each dose will be double checked by two technologists for dosimetry and route of application as per clinical routine. All doses are recorded in the patient notes and the electronic radiology information system (RIS).

Reporting of Adverse events:

Reported adverse events will be recorded and classified and quantified according to the common terminology criteria for adverse events (CTCAE Version 5.0). Such data will be reported in the trial.

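### The by-tracer safety table mixes tracer tolerability with that of furosemide and 1 L of fluid, which go with every 68Ga-PSMA-11 scan and no 18F-PSMA-1007 scan

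*Protocol*

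**What the plan says.** Section 4.4 sets the safety objective in terms of the tracers, and section 5.2 lists as a secondary outcome "Number and severity of adverse events per tracer". Section 11.4.6 gives the analysis: "The number and severity of adverse events (up to 48h post exam) will be summarised by tracer using descriptive statistics". Serious events are listed in addition. No split by cause or by causality rating is described.

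The two examinations differ in preparation. For 68Ga-PSMA-11, section 3.5 says "20mg of furosemide will be given intravenously (i.v.) 20-30 min prior to the final scan", with 1 L of water to drink. Section 6.1 confirms that "furosemide (20 mg 30min before the final scan) and oral hydration (1L) is therefore included in the protocol for" 68Ga-PSMA-11. For 18F-PSMA-1007, section 3.5 says "No further preparations are necessary due to the limited renal excretion of this tracer", and section 6.1 calls furosemide unnecessary.

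On collection and assessment, section 9.2.4 says "Tolerability of the radiotracer will be followed up 48 hours following administration of the radiotracer by the study nurse", with a physician-investigator assessing any event. Section 9.2.4.1 has the clinical notes record "time of onset, duration of event, type of event, symptoms, actions taken" and further items, including the results of any root-cause analysis. Section 10.1.1 defines an adverse event without regard to cause and rates causality with respect to the study drug. Concomitant medication is recorded on the eCRF (section 12.1.2).

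**The concern.** The table is labelled and motivated as tracer safety, but its two columns differ in more than the tracer. One column carries a loop diuretic and a fluid load; the other carries neither. Furosemide is also the one agent given for a pharmacological effect: section 3.7.1 expects none from tracers at these doses, and section 5.4 anticipates no adverse events at all. If tracer events are close to zero, a few cases of dizziness, say, after the diuretic could make up most of the 68Ga column. They would then read as poorer tolerability of 68Ga-PSMA-11. At stake is the interpretation of one descriptive secondary endpoint.

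**Working it through.** The protocol states no adverse event rate, so there is no planned figure to reproduce. The check sets the sections side by side.

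1. **Which scans carry the co-intervention.** Sections 3.5 and 6.1 tie furosemide and 1 L of fluid to 68Ga-PSMA-11 only. With 100 patients completing both scans, that is 100 of 100 68Ga scans and 0 of 100 18F scans.

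2. **Whether the crossover helps.** Section 6.2.1 randomises the order: group A has 18F first, group B has 68Ga first. In both groups the diuretic stays with the 68Ga scan. Randomised order balances period, but tracer and preparation coincide exactly. No contrast in the design isolates either one.

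3. **What enters the table.** Section 10.1.1 counts events regardless of relationship, and section 11.4.6 summarises them by tracer. An event caused by furosemide or fluid within 48 h of the 68Ga scan is therefore counted under 68Ga, whatever its causality rating.

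4. **What the by-tracer difference measures.** Let b be the proportion of patients with an event from any other source, taken as equal for both scans. Let f be the added proportion due to furosemide/fluid, independent of b. Then

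   - 68Ga column: 1 − (1 − b)(1 − f)
   - 18F column: b
   - difference: f(1 − b)

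   Even with equally tolerated tracers, the difference is positive whenever f > 0. The documents give neither b nor f. With assumed values, purely to show the mechanism:

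| assumed b | assumed f | 68Ga, per 100 | 18F, per 100 | difference |
|---|---|---|---|---|
| 2% | 0% | 2.0 | 2.0 | 0.0 |
| 2% | 10% | 11.8 | 2.0 | 9.8 |
| 5% | 0% | 5.0 | 5.0 | 0.0 |
| 5% | 10% | 14.5 | 5.0 | 9.5 |

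   The 0–10% range for f has no source in the protocol. The table shows direction, not an estimate of size.

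5. **What could separate the sources afterwards.** The records in sections 9.2.4.1 and 12.1.2 help an assessor form a view. Concomitant medication shows only that furosemide was given, which is already known for every 68Ga scan. Onset before furosemide rules it out; after that point both agents have been given, and onset alone does not decide. Separation then needs a judgement made when the event is assessed, and section 10.1.1 asks for that judgement on the study drug only.

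**The case against.** The strongest reply is that tracer plus preparation is the comparison that matters clinically. Furosemide is routine with 68Ga-PSMA-11, section 6.1 gives it to make the imaging comparison fair, and all-cause events by procedure received are a conventional safety summary. This stands, provided the table is described that way; the objective, the endpoint and the analysis all describe it as tracer safety.

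A second reply is that attribution is already possible. The causality scale reserves its second-highest grade for events with no other evident cause, and its possible grade allows for one. A physician assesses each event, and root-cause results are recorded. This also stands in part: nothing forces a diuretic effect to be blamed on the tracer. But the planned summary does not use these ratings, and no rating for furosemide/fluid is required.

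A third reply is that table layout belongs in the SAP, which is not shown. That is fair for the extra line. It does not cover the causality item, which section 10.1.1 defines and which has to be collected prospectively. The draft CRF is not shown and might contain such an item, but the protocol text does not require it.

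Patients with a contraindication to furosemide or an eGFR below 35 ml/min are excluded (section 7.1), which should reduce diuretic events without removing the imbalance.

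**Conclusion.** The point holds as a minor one. As written, the safety summary confounds each tracer with its preparation, in a direction unfavourable to 68Ga-PSMA-11. It affects one descriptive secondary endpoint with no test or decision rule. Its size cannot be determined from the documents and may be nil. The primary endpoint, sample size and non-inferiority conclusion do not depend on it.

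Four stronger readings are tempting but not supported:

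- That rating causality only for the study drug is what puts diuretic events under 68Ga. The all-cause tabulation does that. The causality wording only leaves no required rating with which to correct it.
- That the short interval between injection and furosemide, set against 48 h, measures how many events could be separated. It is a share of clock time and says nothing about the number of events.
- That judging expectedness against the radiotracer leaflets is an error. It serves SUSAR classification of the investigational products, and furosemide is not one of them.
- That section 8.7, which anticipates no concomitant interventions, contradicts the furosemide requirement. It can be read as none beyond the scan protocol itself.

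**What to change.** - **Section 10.1.1:** rate causality separately for the tracer and for furosemide/fluid, using the information already recorded under sections 9.2.4.1 and 12.1.2.
- **Section 11.4.6:** report adverse events by tracer overall, and again excluding those attributed to furosemide/fluid. Describe the overall table as a comparison of examination procedures, meaning the tracer plus its preparation.

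The all-cause table should stay, because the second line rests on an open-label judgement of cause and cannot replace it. The cost is one extra assessment item per event and one extra descriptive line. Scans, patient numbers and the primary analysis do not change.
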